### Sample size calculation

The non-inferiority hypothesis is based on the results of a previous study (11). HAMD-17, as the primary outcome, decreased by 11.3 points in the premedication group and by 10.2 points in the EA group, with an equal standard deviation of 11.5 points. Following these parameters, the proposed non-inferiority boundary is set at -4 points, with a level one type I statistical error equivalent to 0.025 and a desired statistical power standing at 80%. These calculations are supported by the analytical tools implemented in PASS 15.0. The results were obtained for a required sample size of 81 cases per group, and considering a 20% drop rate, 102 cases need to be included in each group, totaling 204 cases. The formula employed to determine the sample size in this trial was listed as:

$${\text{n}}_{\text{A}}={\text{k}}_{{\text{n}}_{\text{B}}}\;\text{and}\;{\text{n}}_{\text{B}}=\left(1+\frac{1}{\text{k}}\right){\left(\sigma \frac{Z_{1-\alpha }+Z_{1-\beta }}{\mu_{A}-\mu_{B}-\delta }\right)}^{2}$$

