### Randomization and blinding

This study uses a single-blind design, concealing group allocations from participants. Only acupuncturists will be aware of the assignments, but they will not be involved in any other part of the trial, including enrollment, evaluation, and data analysis. To increase blind validity, treatment will be performed in a separate room. Meanwhile, communication about the treatment or efficacy between acupuncturists and participants will be avoided to the maximum extent. At the conclusion of the 12-week intervention, the Bang blinding index will confirm the effectiveness of the blinding technique (12). The placebo drugs supplied by Shanghai Xinyi Huanghe Pharmaceutical Co. Ltd. have an identical appearance to the proprietary form of ESC (Bailote), which is supplied by Sichuan Kelun Pharmaceutical Co. Ltd. All medications are regularly dispensed once a week, with seven tablets per box. Patients can pick up their medication from the dispenser at their own corresponding number on the pre-packaged envelopes. Before the start of the trial, each investigator will receive multiple training sessions on the implementation of the standards of this study and will strictly adhere to the principle of separation of departments.

The study will use a block randomization method with a block size of four, facilitated by SPSS version 24.0 software. Eligible participants will be randomly assigned to either the EA or ESC group in equal proportions. An independent researcher will enclose the treatment allocation codes in sequentially numbered opaque envelopes, and another independent researcher will assign participants to the groups based on the corresponding number on the pre-packaged envelopes and randomization schedule. To confirm the effectiveness of the blinding, the acupuncturist will inquire with all participants whether they received EA or SA treatment at the end of the trial. All participants’ information will remain confidential to the acupuncturist and assessors throughout the trial.

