### Statistical analysis

Analyses will be conducted on the intention-to-treat (ITT) population, which comprises all qualified participants who meet the inclusion criteria, have received the intervention at least once, and have provided at least one outcome assessment. In statistical analysis, any missing primary outcome data will be replaced by the last observed data point, in accordance with the ITT principle. Additionally, a Per-Protocol Set (PPS) analysis will be employed to assess those participants who completed the trial without significant protocol violations. Data analysis for this study will be performed using the statistical software SPSS V.24.0. Descriptive statistical analysis will be used for all demographic and clinical characteristics of subjects, such as sex, age, and weight. We will validate the homogeneity of demographic characteristics and examine the variables between the two groups. The number of patients who change their medication dosage will also be counted, and the variations between the two groups and within each group will be analyzed. If measurement data follows a normal distribution and has homogeneity of variance, the data values will be reported as mean ± standard deviation (MD ± SD). Covariance analysis will be used to compare the data across different groups. If the data does not adhere to the assumed normal distribution, the median values (P25, P75) will be used to characterize it. The Mann-Whitney U nonparametric test will be used to compare between groups. The mean ± standard deviation will be used for the description of the continuous variables. Qualitative data will be expressed in terms of frequency and percentage. The student’s t-test will be utilized for comparing measurement data between two groups from baseline to the 6-month follow-up, while the rank sum test will be used for ranked data, and the χ2 test will be used for analyzing categorical data. A paired t-test was used for comparisons before and after treatment within a group, and an analysis of variance was used for comparisons among different groups. Repeated-measurement analysis of variance was used to compare groups at multiple observation points. A significance level of 2.5% will be used for all statistical analyses, using two-tailed testing. Subgroup analysis will be conducted to examine differences between different genders and across various age brackets.

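### The sample size rests on a one-sided 0.025 test, but the analysis section sets a two-tailed 2.5% level for every analysis, which read literally halves the error rate for the non-inferiority test

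*Protocol article*

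**What the plan says.** The Hypothesis section makes non-inferiority of electroacupuncture (EA) to escitalopram the trial's claim.

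The Sample size calculation section plans that comparison "with a level one type I statistical error equivalent to 0.025 and a desired statistical power standing at 80" percent. Its printed formula contains "Z_{1-\alpha }+Z_{1-\beta", so the type I error quantile is taken at 1 − α and not at 1 − α/2. The margin is given as follows: "the proposed non-inferiority boundary is set at -4 points". The result is given as "a required sample size of 81 cases per group, and considering a 20% drop rate, 102 cases need to be included in each group, totaling" (the overall figure is 204).

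The Statistical analysis section lists covariance analysis, t-tests, rank tests, χ² tests and analyses of variance, and then says: "A significance level of 2.5% will be used for all statistical analyses, using two-tailed testing". It gives no separate level for the primary non-inferiority comparison.

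**The concern.** A test with α = 0.025 and its quantile at 1 − α is a one-sided 2.5% test, which is the same as comparing one limit of a two-sided 95% interval with the margin. A two-tailed test at 2.5% leaves 1.25% in each tail and corresponds to a 97.5% interval. The analysis sentence covers all analyses and makes no exception, so as written the primary test is held to half the error rate for which the trial was sized.

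Two things are at stake. First, the stated 80% power does not apply to the test as the analysis section describes it. Second, the same data could meet the margin under one section and miss it under the other. An unsettled level leaves room to choose between the 95% and the 97.5% interval after the data are seen.

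**Working it through.** **Inputs** (Sample size calculation; allocation from Randomization and blinding). SD 11.5 in both arms; reductions of 11.3 (drug) and 10.2 (EA); margin −4; power 80%; 1:1 allocation; 20% dropout.

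**Step 1: reproduce 81.** With A = drug, B = EA, k = 1 and δ = −4, the denominator of the printed formula is 11.3 − 10.2 + 4 = 5.1. Then n per group = 2 × [11.5 × (z₁₋α + 0.842) / 5.1]².

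| Level | z | n, normal formula | n, t-test |
|---|---|---|---|
| one-sided 0.05 | 1.645 | 63 | 64 |
| one-sided 0.025 | 1.960 | 80 | **81** |
| two-tailed 0.025 (0.0125 per tail) | 2.241 | 97 | 98 |

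Only one-sided 0.025 gives 81. Then 81 / 0.80 = 101.25, rounded up to 102 per group and 204 in total, as stated. The plan was therefore sized at one-sided 0.025, although the words do not appear.

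**Step 2: apply the analysis rule.** The critical value becomes 2.241 in place of 1.960. The standard error is SE = 11.5 × √(2/n). Half-widths use the normal quantile; power is from the noncentral t distribution at distance 5.1.

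| Analysed per arm | SE | Half-width, one-sided 0.025 | Half-width, two-tailed 2.5% | Power, one-sided 0.025 | Power, two-tailed 2.5% |
|---|---|---|---|---|---|
| 81 | 1.807 | 3.54 | 4.05 | 80.1% | 71.2% |
| 102 | 1.610 | 3.16 | 3.61 | 88.3% | 81.8% |

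**Step 3: when does an observed difference of zero fail?** It fails when the half-width exceeds 4, that is when n < 2 × (2.241 × 11.5 / 4)² ≈ 83.0. At n = 83 the half-width is 4.001 and at n = 84 it is 3.98. With t quantiles it is 4.01 at 84 and 3.99 at 85. The threshold is therefore about 83 to 84 analysed per arm. Under one-sided 0.025 a zero difference passes even at 81, since 3.54 < 4.

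**Step 4: what would the stricter level need?** 98 per group for 80% power, and 98 / 0.80 = 122.5, so 123 per group or 246 in total, against the planned 204.

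**The case against.** **The authors probably meant 2.5% per tail.** That would equal two-sided 5% and match the sample size. It is plausible, but it is not what the sentence says, and the same correction would still be needed.

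**The section names no confidence interval and no non-inferiority test.** This is correct. The 97.5% interval is the consequence of applying the sentence literally, not something the article spells out. A separate analysis plan may describe the margin test, but it would have to depart from the published sentence to agree with the sample size.

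**The stricter level is conservative.** It is: it cannot raise the risk of a false non-inferiority claim. That limits the harm but does not remove the contradiction.

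**The analysed number may exceed 81.** This objection stands, and it limits the size of the point. A reader might infer that the trial falls below 80% power, or that a zero difference would fail, whatever the analysis set. The documents do not support that. The intention-to-treat set keeps anyone treated at least once with at least one outcome assessment, and missing primary values are filled with the last observation. Up to 102 per arm could be analysed. At 102, power is 81.8% on these inputs and a zero difference passes.

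**Two further readings should also be resisted.** A reader might quote the drop from 35.8% to 25.8% power at 81 per arm that follows if EA is 1.1 points worse, as the article's figures say. Most of that shortfall is a separate matter: the calculation that reaches 81 counts the 1.1 points in EA's favour. It should not be used to size this point. A reader might also infer that a two-sided 2.5% level for secondary comparisons is an error. It is unexplained, but it is a permissible choice.

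**Conclusion.** The point holds as a contradiction between two sections about the level of the primary test. The sample size section uses one-sided 0.025; the analysis section, read literally, uses 0.0125 in the relevant tail.

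The cost on the inputs that reproduce 81 is about 9 percentage points of power at 81 evaluable per arm (80.1 − 71.2 = 8.9), which takes the trial below its stated 80%. It is about 6.5 points at 102 (88.3 − 81.8), which leaves it just above. The decision on a zero observed difference changes only at about 83 to 84 or fewer analysed per arm, a range that includes the planned 81.

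These figures assume an SD of 11.5, a distance of 5.1 points to the margin, equal arms and an unadjusted comparison of means. They take the 5.1 as the plan used it and do not endorse it.

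**What to change.** In the Statistical analysis section, state that non-inferiority on the change in HAMD-17 from baseline to week 12 is tested at one-sided 2.5%, by comparing the relevant limit of the two-sided 95% confidence interval with the 4-point margin. Remove the primary comparison from the blanket two-tailed 2.5% sentence. State the level for secondary and subgroup comparisons separately; whether that is 2.5% or 5% two-sided is for the sponsor to decide.

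The cost is a sentence or two, settled before unblinding. On the plan's own calculation, 81 evaluable and 102 randomised per group remain as they are. If the sponsor does intend two-tailed 2.5% for the primary test, the sample size section should say so and be recalculated: 98 evaluable per group, 246 in total after 20% dropout, on the same inputs.

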### Patient and public involvement

Patients with mild to moderate depression in the clinical department were consulted by the main researcher before the trial design. The treatment frequency and duration of this study were summarized from clinical experience and patients’ feedback. We will recruit all participants from the outpatient clinics in four centers. Patients who were involved in the consultation about the trial design before will not be recruited as participants. A journal article manuscript will be written to present the results after the trial completed, and a brief summary of results with plain language will be sent to all participants. The burden of intervention will not be assessed by participants themselves.

### Ethics and dissemination

All acupuncturists are licensed physicians with at least 3 years of experience in acupuncture treatment. They will participate in clinical training to ensure that EA and SA practices are standardized prior to the intervention.

To guarantee strict quality control during the implementation of the study and to ensure the reliability and reproducibility of the trial results, the project will establish a DSMB consisting of a professional in clinical research of acupuncture ([name]), a psychiatrist ([name]), and a statistician ([name]). The DSMB will monitor whether the trial complies with the study design and standard guidelines or not. The DSMB will hold regular meetings to request progress reports from investigators and provide professional guidance and solutions to issues that may arise during the trial.

## Discussion

An epidemiological study of people with depression over a 12-month period found that 26.6%, 53.4%, and 20.0% were classified as having mild, moderate, and severe depression, respectively (20). Failure to promptly relieve the depressive state and its accompanying symptoms during early episodes of depression can contribute to its aggravation or recurrence, leading to impaired functioning, reduced productivity, and an increased risk of suicide, which can ultimately result in significant public health and economic consequences (21, 22). The question we put forward in this clinical trial is whether EA is not inferior to ESC for treating mild to moderate first-episode depression. ESC has high efficacy and favorable acceptability in patients with depression in China (23–25). By utilizing an established and effective SSRI as a positive control, we can more precisely evaluate the potential benefits and risks of the novel treatment (EA) in comparison to the standard-of-care therapy (ESC). However, the delayed onset of antidepressant action can prolong patients’ depressive feelings. AEs may also hinder therapeutic effects and result in high dropout rates, which leads to a large proportion of depressed patients who struggle to achieve complete remission and experience relapse. Thus, it is imperative to explore alternative or complementary treatments for depression, particularly in the early phase of the disease (26).

EA treatment can adjust the overall nervous, endocrine, and immune systems of the body across multiple levels, control the depressive emotions and somatization symptoms of patients with depression, and have the advantages of few side effects and long duration (27–29). Furthermore, EA offers a non-pharmacological alternative to traditional antidepressants, which could be particularly beneficial for patients who experience side effects or prefer non-drug treatments. Moreover, previous studies (9) have shown that EA treatment has a faster onset of action compared to SSRIs and functions as a safer complementary therapy. Nonetheless, the quality of evidence supporting the efficacy and safety of EA in treating depression remains at a low-to-moderate level. Most of these clinical trials had a high risk of bias, thus calling for rigorous randomized controlled trials. Besides, there are few clinical studies about EA treatment for the treatment of first-episode depression. The antidepressant effect of EA has not been previously proposed, but it may be associated with inhibiting hypothalamic-pituitary-adrenal (HPA) axis hyperactivity, regulating neuropeptides and neurotransmitters, decreasing proinflammatory cytokine levels, and restoring hippocampal synaptic plasticity, among other mechanisms (28).

Traditional Chinese medicine (TCM) theory states that depression is mainly caused by ‘qi’ stagnation, which subsequently leads to the disorder in the brain’s qi systems and an imbalance of yin and yang. In this trial, we will apply a semi-standard point selection consisting of core and additional acupoints, strictly following the syndrome differentiation of TCM theory and allowing some flexibility based on the individual patients’ specific symptoms. The Governor Vessel connects the brain directly and is commonly used to treat depressive disorders (30, 31). GV20 and GV29 are often used to promote the recovery of depressive disorder, as they may facilitate the flow of qi and blood in the brain and restore brain function by ameliorating cognitive deficits (28, 32). The Ren Meridian, has the same origin as the Governor Vessel Meridian. RN6 and RN4, together with ST36 and SP6, can supplement the deficiency and drain the excess, tonifying Qi and blood and relaxing the patient (33), thus regulating the somatization symptoms in conjunction with the Governor Vessel as a whole. In addition, based on the clinical experience of many professional acupuncturists and our previous clinical studies (29, 34), the acupoints we applied effectively improved poor minds and relieved depressive symptoms. The long-range effect is also an important factor of acupuncture treatment, and thus we set long enough intervention period and follow-up period. It will be possible to investigate the enduring effects of acupuncture on depression and ascertain the duration of the therapeutic effect. However, there are still several challenges and limitations in this study. Firstly, it is not feasible to achieve blinding of the acupuncturists during the intervention period, and thus rigorous training will be provided to minimize any potential bias. Acupuncturists will not be involved in either assessing patients or the analysis. Secondly, we are concerned that the initial clinical dose of ESC (10mg) was not effective in relieving depressive symptoms in some patients and therefore allowed them to increase the dose (up to 20 mg) according to their symptoms under the guidance of their psychiatrists. Increasing the drug dose may provide more effective clinical benefits to patients, but at the same time, we cannot be sure whether the changes brought about by the dose of the drug are due to purely time effects or a cumulative dose effect. Thirdly, the outcome of this study was subjective and vulnerable to reporting bias. Further studies should focus on precise objective outcome assessment. Finally, we set a 12-week follow-up time, which may lead to an increased dropout rate. Therefore, more flexible approaches should be employed during the follow-up period, such as making online inquiries or evaluating by phone.

## Conclusion

In summary, we will strictly adhere to the CONSORT statement and STRICTA recommendations to ensure standardized acupoint selection, manipulation, evaluation, and therapist clinical experience. As a multi-center RCT in a first-line city, we expect that this trial will validate the effectiveness and safety of EA as a clinical intervention for mild to moderate first-episode depression, which will address the gap left by SSRIs and provide a low-risk, beneficial non-drug therapy for patients with depression.
